The key objectives are to determine whether the POI ‘Sleep intervention’ or ‘FAB intervention’ from late pregnancy to 2 years of age result in differences in:BMI z-score at 3.5 and 5 years of age (primary objective)Self-regulation (overall, sleep-related, or energy) at 3.5 and 5 years of ageOther weight indices (BMI, prevalence of overweight or obesity, waist circumference) at 3.5 and 5 years of ageBody composition at 5 years of ageSleep (timing, duration, awakenings, problems) at 3.5 and 5 years of agePhysical activity at 3.5 and 5 years of ageDiet at 3.5 and 5 years of age.

Additional objectives include determining, in a cohort analysis, possible predictors of BMI, self-regulation (overall, sleep-related, energy), and sleep consolidation (timing, duration, awakenings, problems) at 3.5 and 5 years of age.

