#### Anthropometry (objectives a and c)

Trained measurers will conduct all anthropometric measurements following standard protocols [82]. Weight will be obtained with children wearing standard clothing (singlet and underwear) using regularly calibrated electronic scales (Tanita WB-100 MA/WB −110 MA). Height will be measured using a Harpenden stadiometer (Holtain Ltd, UK). Waist circumference will be measured at the minimum circumference between the rib cage and the iliac crest using a Rosscraft Anthropometric tape (Rosscraft Innovations Inc, USA). A third measurement will be made if duplicate measures are not within 0.1 kg for weight, 0.7 cm for height, and 1.0 cm for waist circumference (with the mean of the two closest measurements used in such cases) [38]. Weight-for-age z-score and BMI-for-age z-scores will be calculated using the WHO growth standards [83], with overweight defined as a BMI-for-age z-score ≥85th to <95th percentile and obesity defined as ≥95th percentile.

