### Analysis

For the key objectives, data will be analysed using linear, logistic (binary or ordinal), and Poisson (or negative binomial) regression models to compare the four arms of the trial in terms of continuous, categorical (binary or ordinal), and count outcomes respectively, with a random effect for participant along with terms for age and a group-by-age interaction added when longitudinal outcomes are analysed. As analyses at 2 years did not find consistent evidence in support of interactions between the Sleep and FAB interventions, we also plan to investigate outcomes using combined Sleep and combined FAB groups. A two stage process will be used, first investigating whether there is evidence for such an interaction (a reparameterisation of the four group model) and if not, the Sleep and FAB intervention terms will be investigated without the interaction included, although this process will increase the Type I error rates beyond the nominal level [101]. All *P*-values will be reported using three decimal places and *p*-values less than 0.001 will be reported as ‘*p* < 0.001’. Two-sided *p* < 0.05 will be considered to indicate statistical significance and no adjustments for the multiple outcomes are planned. Post-hoc comparisons between the three intervention and one control groups will only be performed where the overall (Wald) test is statistically significant. Where available, baseline values will be included in models and all models will include the stratification variables [102]. Standard model diagnostics will be used and log-transformations used where this improves residual normality and/or homoscedasticity for continuous outcomes. Homser-Lemeshow tests will be used for binary logistic regression models and proportionality will be assessed in ordinal logistic regression models using generalised ordinal logistic regression. Overdispersion will be examined using a likelihood ratio test for count outcomes, with negative binomial regression used when this is significant. Where model residuals remain unacceptable for continuous outcomes, quantile regression, including mixed quantile regression where appropriate, will be used instead to model medians.

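### For continuous outcomes measured at both ages, the stated random-effect model, as ordinarily fitted, uses one pooled variance for the arm contrasts at 3.5 and 5 years; the plan should let the variance differ by age

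*Protocol article*

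**What the plan says.** The Analysis section states that "data will be analysed using linear, logistic (binary or ordinal), and Poisson (or negative binomial) regression models" to compare the four arms, "with a random effect for participant along with terms for age and a group-by-age interaction added when longitudinal outcomes are analysed". It names no residual variance structure, so it neither imposes a common variance at the two ages nor provides for different ones.

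It does say what happens if the model fits badly: "Standard model diagnostics will be used and log-transformations used where this improves residual normality and/or homoscedasticity for continuous outcomes". After that, "Where model residuals remain unacceptable for continuous outcomes, quantile regression, including mixed quantile regression where appropriate, will be used instead to model medians". A variance that depends on age is not among the listed steps.

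The key objectives, at the end of the Background, ask for effects at 3.5 and 5 years. The primary one is BMI z-score. The Anthropometry section says "Weight-for-age z-score and BMI-for-age z-scores will be calculated using the WHO growth standards", so the primary outcome is standardised for age. Raw BMI and waist circumference are also objectives at both ages.

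**The concern.** With two visits, a linear model with a participant random intercept and one residual variance implies the same total variance at both ages. Several continuous outcomes are not scaled for age: raw BMI, waist circumference, accelerometer counts per minute, and task scores that are not age-normed. Children grow and mature between 3.5 and 5 years, so equal spread at the two ages cannot be taken for granted.

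If the spread differs, the standard error of the arm contrast is wrong at each age, in opposite directions. One age has too many false positives and the other loses power. These age-specific contrasts are what the objectives ask for. The remedies on the page do not target this cause, and both change the quantity estimated: a log-transform turns a difference in means into a ratio of geometric means, and quantile regression gives a difference in medians.

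**Working it through.** **Figures in the plan.** The article gives no figure for this point. The nearest is the power statement under Sample size, which rests on a single SD of 0.8 kg/m² with no split by age. Assuming equal arms, 600/4 = 150 per arm. The standard error is 0.8 × √(2/150) = 0.0924, 0.3/0.0924 = 3.25, and power is Φ(3.25 − 1.96) = 90%. The stated 80% needs only 112 per arm. The stated power is therefore conservative, and nothing below depends on it.

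**Inputs.** Two visits, the random-effect model and a two-sided 0.05 level come from the Analysis section. The SD ratio k (larger over smaller, after covariate adjustment) is assumed, because the article gives no SDs by age.

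**Formulas.** Let the true variances be s² at one age and k²s² at the other. With both visits complete, the random-intercept model fits a total variance of s²(1 + k²)/2 at both ages. Model SE over true SE is then

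- at the age with larger spread: √[(1 + k²)/(2k²)]
- at the age with smaller spread: √[(1 + k²)/2]

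The number per arm cancels. With f as this ratio, type I error is 2[1 − Φ(1.96 f)]. For a contrast that would have 80% power with the correct SE, power is Φ(2.80 − 1.96 f).

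**Example, k = 1.2.** (1 + 1.44)/2 = 1.22. Larger spread: √(1.22/1.44) = 0.920, 1.96 × 0.920 = 1.80, type I error 7.1%. Smaller spread: √1.22 = 1.105, 1.96 × 1.105 = 2.17, type I error 3.0%.

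| SD ratio k (assumed) | SE ratio, larger spread | Type I error | 95% CI coverage | SE ratio, smaller spread | Type I error | Power (80% if SE correct) |
|---|---|---|---|---|---|---|
| 1.0 | 1.000 | 5.0% | 95.0% | 1.000 | 5.0% | 80% |
| 1.1 | 0.956 | 6.1% | 93.9% | 1.051 | 3.9% | 77% |
| 1.2 | 0.920 | 7.1% | 92.9% | 1.105 | 3.0% | 74% |
| 1.3 | 0.892 | 8.0% | 92.0% | 1.160 | 2.3% | 70% |
| 1.5 | 0.850 | 9.6% | 90.4% | 1.275 | 1.2% | 62% |

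**Simulation.** In 20,000 simulated four-arm trials with 150 per arm, type I error was 7.1% and 3.2% at k = 1.2, and 9.7% and 1.3% at k = 1.5. Shorter runs of a fitted random-intercept model (250 per setting) were noisier but showed the same direction. At k = 1.25 the SE ratios were 0.91 and 1.07, against 0.91 and 1.13 by formula.

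**What is not affected.** The group-by-age interaction depends on the variance of the within-child change, which this model fits correctly for complete pairs (simulated type I error 4.8%). The problem is confined to the age-specific contrasts.

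**What the log-transform does.** To first order the SD of log Y is SD/mean, so the SD ratio after logging is about k/m, where m is the ratio of the two means. It becomes 1 only if m = k. With k = 1.2 and m = 1.2 the problem goes. With k = 1.2 and m = 1.0 the ratio stays at 1.2 and type I error at 7.1%. With m = 1.1 it is 1.2/1.1 = 1.09, close to the 1.1 row.

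**The case against.** The best reply is that the article does not commit the trial to a common residual variance. An age-specific variance is compatible with its wording, and a journal article may leave that detail to an analysis plan. This stands as far as it goes. A reader might infer that the plan forces equal variances and so will produce false positives at 5 years, but the documents support neither step. The structure is not stated, and nothing shows that any outcome's spread grows with age. The dietary questionnaire and the nap rules do differ between the ages, which makes equal spread less certain but does not show which way it would go. What remains is that the article sets out its own sequence for unequal variance, and that sequence omits the remedy that fits this cause.

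Other replies also stand in part:

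- The random effect enters only when both ages are modelled together. A regression at a single age has no such pooling.
- The plan does check homoscedasticity, and the log-transform works when SD rises in proportion to the mean. It does not work otherwise.
- The primary outcome is age-standardised, and binary, ordinal and count outcomes have no free residual variance of this kind. This stands in full and limits the reach of the point.
- The error rates above are for one ungated contrast, whereas pairwise comparisons follow only a significant overall Wald test. They are therefore not the error rates of the whole procedure. The gate would not remove the problem if it is the three-degree-of-freedom group test at the age with larger spread: that test would reject in 6.8% to 10.1% of null cases for k from 1.1 to 1.3. The article does not say at which age, or over both, the overall test is made.

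It is also tempting to say that the log and median fallbacks should be dropped. The documents give no ground for that; they remain reasonable for non-normal residuals.

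**Conclusion.** The point holds as a minor one. As ordinarily fitted, the stated model gives age-specific intervals that are too narrow at one age and too wide at the other for any continuous two-age outcome whose spread differs by age. For SD ratios of 1.1 to 1.3, type I error is about 6% to 8% at the age with larger spread and about 4% to 2% at the other. This rests on three assumptions: one residual variance, an SD ratio in that range, and near-complete pairs of visits. The documents confirm none of the three. The result is a range of possible distortion in secondary raw-scale outcomes and does not demonstrate an error. The primary BMI z-score is little affected if its SD is similar at both ages.

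**What to change.** For continuous outcomes measured at both ages, replace the participant random intercept with an unstructured 2x2 residual covariance across the two visits. Keep the age and group-by-age terms and take each age's contrast from that model. The random intercept has to go because it would be redundant beside an unstructured covariance. Try this before the log-transform or median regression, and keep those two for residuals that are not acceptably normal. Use the same structure in the multiple-imputation sensitivity analyses.

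The cost is one extra variance parameter (three instead of two), a line of model syntax in Stata or R, and no new data. If the spread turns out equal at the two ages, almost nothing is lost.

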In 2009, we commenced the POI (Prevention of Overweight in Infancy) RCT in 802 Dunedin families designed to reduce the number of children with excessive weight gain in the first 2 years of life [38]. Participants were randomised to one of four groups: Control (usual care), FAB (food, physical activity and breastfeeding), Sleep, or Combination (received FAB and Sleep interventions). All four groups received standard Maternity and Well Child care [39], and the three intervention groups received additional guidance and support on the relevant behaviours (breastfeeding, diet, physical activity, sleep) as detailed previously [38, 40, 41]. The POI study, and the three large controlled trials from Australia (Healthy Beginnings [42], Nourish [43], and InFANT [44]), are combining their data to form a prospective meta-analysis of the feasibility and effectiveness of early obesity prevention efforts (Early Prevention of Obesity in Children, EPOCH) [45]. Care has been taken to ensure that the study design, participants, intervention, comparators and outcome measures are similar across all four studies.

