### Sample size

Retention at 2 years was 86 % (*n* = 686/802) which is higher than was anticipated in our original power calculations (20 % loss to follow-up was assumed) [38]. Based on this, we anticipate retaining at least 75 % of the original cohort through to age five, giving us an estimated sample size at 5 years of at least 600 participants. This would provide 80 % power to detect a difference in BMI of 0.3 kg/m^2^ or larger at 5 years of age between any pair of the four groups using a two-sided test at the 0.05 level, based on earlier data from this research group suggesting a standard deviation of 0.8 [49]. This sample size would also allow 80 % power for detecting differences in self-regulation scores of 0.35 standard deviations between any two arms of the trial (falling between a “small” and “moderate” effect size) and detecting correlations at the study level of 0.12 or larger between continuous measures (e.g. between parenting style at 12 months and self-regulation at 5 years and between consolidated sleep hours at 6 months, and self-regulation at 3.5 and 5 years) using two-sided tests at the 0.05 level.

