Similar models will be used for the additional objectives with the study group included but not of direct interest in itself. No subgroup analyses are currently planned. All effect sizes will be accompanied by 95 % confidence intervals and these will be used to assess clinical significance alongside determination of statistical significance. As missing data is expected to be around a quarter of the original participants and is unlikely to be MCAR or even MAR when conditioning only on the intervention group and stratification variables alone, all analyses will be accompanied by sensitivity analyses using multiple imputation with predictors including previously available outcome measures where possible and using chained equations when necessary. Rubin’s method for combining the results from the 25 imputations (or more if necessary such that the number of imputations exceeds the percentage of missing data) will be used. Scenario analyses will be performed to explore the robustness of findings to models of informative missingness [103]. Current or subsequent versions of Stata (14.1 or later) and R (3.3.1 or later) will be used for all analyses. Statistical analyses will be conducted by one of the co-investigators (AG) who also performed analyses on outcomes at earlier times.

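### As written, the overall Wald test decides whether arm-versus-control differences are produced at all, when it need only decide whether they are called significant

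*Protocol article*

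**What the plan says.** The trial has four arms: "Participants were randomised to one of four groups: Control (usual care), FAB (food, physical activity and breastfeeding), Sleep, or Combination". The Analysis section compares them with regression models and then sets this condition: "Post-hoc comparisons between the three intervention and one control groups will only be performed where the overall (Wald) test is statistically significant". The significance rule is "Two-sided *p* < 0.05 will be considered to indicate statistical significance and no adjustments for the multiple outcomes are planned".

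Three other statements bear on it.

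- Later in the Analysis section, effect sizes are to carry 95% "confidence intervals and these will be used to assess clinical significance alongside determination of statistical significance".
- The Sample size section plans to "detect a difference in BMI of 0.3 kg/m^2^ or larger at 5 years of age between any pair of the four groups", with 80% power and an SD of 0.8.
- The Analysis section also plans combined Sleep and combined FAB comparisons. Whether these are fitted without an interaction term depends on a check for interaction, not on the overall Wald test.

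**The concern.** The condition attaches to carrying out the comparison, not to declaring it significant. Nothing else in the article says that the three arm-versus-control differences will be given when the overall test is not significant.

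Two things are at stake. First, an interval is most useful when a test is non-significant: it shows whether an effect of the planned size has been ruled out or is still open. The rule withholds the arm-level interval in exactly that case. Second, if arm differences appear only when the four means happen to be well spread, the ones that appear are on average too far from zero. No adjustment for multiple outcomes is planned, so this selection repeats outcome by outcome.

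**Working it through.** **Inputs.** From the Sample size section: at least 600 children at 5 years (75% of 802 = 601.5), SD 0.8, difference 0.3 kg/m², two-sided 0.05, power 80%. Assumed: equal arms of 150 (the article gives no allocation ratio), a normal outcome, one time point and no covariate adjustment.

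**1. The plan's own figure.** The pairwise standard error is 0.8 × √(2/150) = 0.092. Power for 0.3 is then 90.1%, not 80%; 80% needs 112 per arm (448 in all), and the difference detectable with 80% power at 150 per arm is 0.26. The stated 80% is therefore conservative, and nothing below depends on it.

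**2. The withheld interval.** Half-width = 1.96 × 0.092 = 0.18 kg/m². An observed difference near zero would exclude 0.3. With no true effect in any arm and a non-significant overall test, the withheld Sleep-versus-Control interval excludes a 0.3 reduction in 91% of simulated trials.

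**3. Selection.** 400,000 four-arm trials were simulated per scenario. The overall test is a 3-df F test at 0.05, which is close to the Wald test: F = 150 × variance of the four arm means ÷ pooled residual variance. The table gives the difference from Control for an arm with a true effect, averaged over trials in which the overall test was significant.

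| True reduction (kg/m²) | Arms affected | No arm contrast | Mean reported reduction | Inflation | Coverage of 95% CI |
|---|---|---|---|---|---|
| 0.10 | one | 83% | 0.191 | 91% | 84% |
| 0.10 | both Sleep-containing | 78% | 0.174 | 74% | 87% |
| 0.15 | one | 65% | 0.221 | 47% | 92% |
| 0.15 | both | 54% | 0.201 | 34% | 93% |
| 0.20 | one | 41% | 0.246 | 23% | 95% |
| 0.20 | both | 27% | 0.228 | 14% | 95% |
| 0.30 | one | 7% | 0.310 | 3% | 96% |
| 0.30 | both | 2% | 0.303 | 1% | 95% |

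With no true effect anywhere, the contrasts appear in 5% of trials. Their mean absolute size is then about 0.145, and the nominal 95% intervals cover about 62% of the time. Reported without the condition, the same estimates are unbiased with 95% coverage in every scenario.

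**4. What the pooled terms supply.** The pooled Sleep term is half of (Sleep + Combination − Control − FAB), with half-width 1.96 × 0.8 × √(1/150) = 0.128. The article gives no threshold for the interaction check; 0.05 is assumed.

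- True −0.15 in both Sleep-containing arms: the pooled term is available in 95% of trials, averages −0.150 and has 95% coverage. Only 0.8% of trials have neither a pooled nor an arm estimate.
- True −0.15 in the Sleep arm alone: the pooled Sleep term is (−0.15 + 0 − 0 − 0)/2 = −0.075, half the arm effect. The pooled FAB term is (0 + 0 − 0 + 0.15)/2 = +0.075, although FAB does nothing. In 5.4% of trials there is neither estimate.

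**5. The condition as a testing rule.** With no true effect, it cuts the chance of any false arm-versus-control result from 12.5% to 4.0%. For a true 0.3 in one arm, pairwise power falls from 90.0% to 87.3%, still above the planned 80%.

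**The case against.** The strongest reply is that the sentence follows directly on the significance threshold and describes an ordinary protected test. The four-group model yields the arm coefficients anyway, the article attaches intervals to all effect sizes without a condition, and the layout of results tables may be settled in a fuller plan. The key objectives in the Background concern the Sleep and FAB interventions, which the pooled terms address directly.

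Much of this stands. As a testing rule the condition is legitimate. A reader might infer that null outcomes get no effect estimate at all; the article does not support that, because the pooled terms are not tied to the overall test. A reader might also infer that every reported arm effect is materially inflated; at the planned 0.3 kg/m² the inflation is only 1–3%. Nor does the condition undermine the planned power.

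What does not stand is that the interval sentence cures the problem. It says that effect sizes carry intervals, not which effects are reported, while the earlier sentence says that these comparisons are not made. Nor do the pooled terms replace arm contrasts when the interventions do not act additively. A 3-df test can be non-significant while the interaction check is positive, and the article then specifies neither kind of estimate. Effects below 0.3 are also plausible: the Background reports that two of three comparable trials found no significant BMI effect and that the third's benefit was no longer apparent at 5 years.

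**Conclusion.** The point holds in limited form. The article makes a significance test decide whether arm-versus-control differences are produced, in tension with its own use of intervals and with sizing "between any pair of the four groups using a two-sided test at the 0.05 level". The loss is of arm-level estimates for outcomes with a non-significant overall test, not of all estimates. The selection bias is negligible at 0.3 kg/m², moderate at 0.20 (14–23%) and large at 0.15 and below (34–91%).

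The figures rest on equal arms of 150, an SD of 0.8 and an unadjusted comparison of raw BMI at one age. The primary outcome is BMI z-score, and the planned models add stratification variables, baseline values where available and repeated measures. The sizes are therefore indicative; the direction does not depend on these details.

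**What to change.** Replace the conditional sentence with wording such as: *The three intervention-versus-control differences from the four-group model will be reported with 95% confidence intervals for every key outcome, whatever the result of the overall test. A pairwise difference will be called statistically significant only if the overall Wald test is also significant.*

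The cost is one sentence and longer results tables. The differences are already coefficients of the fitted model, so no new analysis is needed.
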